**25.b Primary outcome**

Further details on assessment are provided in protocol and Appendix 3.

**25.c Secondary outcomes**

Major secondary outcomes have been defined in Appendix 3.

**26. Analysis methods****26.a Primary analysis methods used for the primary outcome**

The primary analyses will be the estimation of the effect of the intervention on substance use disorders in high-risk youth in intervention conditions relative to their control counterparts, at the year 5 follow-up (48 months post-intervention). The odds ratio (OR) will be used as the measure of intervention effect for the binary substance use disorders outcome. To account for within-cluster (school) variance, intervention effects will be examined using hierarchical generalized linear modelling (HGLM; using the SAS program, Proc GLIMMIX) using a Bernoulli distribution for the binary primary outcome. The HGLM model will be two-levels, with students as the first level, and nested within schools (clusters) as the second level of the model.

**26.b Supplementary analysis methods used for the primary outcome**

Similar to the primary analysis, supplementary analysis will be done on the binary primary outcome (substance use disorders) over all post-intervention time points (12 - 48 months), to estimate the effect of the intervention on substance use disorders in high-risk youth in intervention conditions relative to their control counterparts over the 5-year trial (i.e. growth in substance use disorders). To account for within-cluster (school) variance, intervention effects will be examined using HGLM, and the outcomes will be centered at the 12-month follow-up to allow for comparisons between groups post-intervention. The model will be three-levels, with time points as the first level, nested within students as the second level, nested within schools as the third level of the model. When significant effects are revealed on growth, analyses will be conducted (i.e. HGLM) testing intervention effects on onset of use at specific time points while controlling for cluster, using tests based on the Huber-White sandwich estimate of variance.

Supplementary analysis will also be done on the estimation of the effect of the intervention on the continuous value of the primary outcome measure (DEP-ADO scores) between control and intervention group, at the year 5 follow-up (48 months post-intervention). Effect will be analyzed using a mixed effect linear model to compute adjusted mean difference between arms along with their standard errors. The model will be two-levels, with students as the first level, nested within schools as the second level of the model. If there is a violation of distribution assumption on outcomes, appropriate transformation will be used.

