Primary outcomes are on the intent to treat sample of youth who meet high risk (HR) personality criteria. To account for within cluster (school) variance, intervention effects will be examined using hierarchical generalized linear modelling (HGLM; using the program HLM 6) [111, 112] using a Bernoulli distribution for the binary primary outcome. Secondary outcome variables will be centred at the 12-month post-test to allow for comparisons between groups (intervention vs. control) after the intervention, and growth terms will be used to detect prevention effects on growth of onset of target behaviour over four years. For the three drinking outcomes, unconditional models from previous trials revealed that more than 10% of systematic variance existed at the between-school level (25-27%), therefore, HLM with robust standard errors will be used to assess intervention effects on the 12-month intercept and growth in drinking from 12-48 months [111]. When significant effects are revealed on growth, STATA (StataCorp, College Station, TX) will then be used to conduct logistic regression analyses testing intervention effects on onset of use at specific time points while controlling for cluster, using tests based on the Huber-White sandwich estimate of variance [110]. The illicit drug use outcome, problem drinking outcomes and cognitive outcomes are not expected to have high inter-class correlations [29]; HGLM will be used to conservatively assess these outcomes, nevertheless. We will also report cluster-level analyses in which individual-level variability is removed and analyses are conducted at the school-level, comparing mean outcomes for intervention (n=15) and control schools (N=15) using one-way repeated measures design with time as repeated measures and intervention as a fixed independent variable following recommendations by [113]. Path analyses will investigate mediational role of substance use and cognitive outcomes risk for addiction.

*2.17 What is the proposed frequency of analyses?*

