## 10. Sample size calculation for the primary outcome

Sample size calculations are conducted according to the sample needed for the primary long-term analyses, namely the onset of substance use disorders 4-years post-intervention in the sub-group of students identified at high-risk in grade 7. As the school (cluster) is the unit of randomisation, the sample size determination accounts for the clustering of students within schools. According to data from a local epidemiologic study and a previous personality-targeted intervention trial, the expected proportion of students with a substance use disorder in grade 11 in the control group is 10%. The minimum detectable reduction is set to 50% (i.e., 10% substance use disorders in grade 11 in the control group versus 5% in the intervention group). Assuming that this proportion per school is approximately normally distributed (i.e., 95% of the schools would fall within two standard deviations of the mean, 10%, 7 %), we obtain a between-cluster coefficient of variation,  $k$ , of 0.35. In addition, we expect 50 students per school (40-45% of the full sample) to be identified as high-risk (average cluster size of 50), following previous personality-targeted intervention studies. With these assumptions (using formula 7.7,), the number of schools (clusters) per arm needed to detect a 50% reduction in the proportion of drinkers (i.e., from 10% to 5%) with 80% power and a false positive error rate of 2.5% is 15, giving a total of 30 schools or approximately 1500 high-risk students. We plan to recruit two additional schools ( $30 + 2 = 32$  schools total) to account for potential attrition at the school-level.

For the secondary outcomes (other measures of substance use, mental health and cognition), we will use the observed effect sizes from the IMAGEN study on 2000 14 year-old European participants who completed neuropsychological assessments. Binge drinkers showed reduced IQ and a greater reward bias on the Passive Avoidance Learning Paradigm^45 relative to non-bingers where observed effect sizes ( $d$ ) for these mean differences ranged

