**15. Confidence intervals and p-values**

All applicable statistical tests will be two-sided and at the 5% significance level, unless otherwise specified, with two-sided 95% confidence intervals presented whenever possible.

**16. Description of any planned adjustments for multiplicity, and if so, including how the type 1 error is to be controlled**

As there is a single primary endpoint, and the secondary endpoints are to be used only in providing additional supportive exploratory information, and no interim analysis on the primary outcome were done, there will be no adjustments for multiple testing.

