**20. Reporting of screening data to describe representativeness of trial sample**

Co-Venture cohort, which includes 76% of all grade 7 students attending 31 secondary schools in the greater Montreal area (Quebec, Canada). This cohort represents 15% of all schools in the area and each of their respective school districts in size and deprivation indexes within 1.5 standard deviation.

Quality control is conducted using both automated algorithm-based functions and manual scanning of data. The DMC provides coded databases to study research assistants and PHD students responsible for data quality control and will oversee all quality control protocols.

We have developed a successful automated system for data quality control which included sham questions ([name] et al., 2010), questions on participant motivation (Seguin, et al., (2009) and testing context (Schumann, et al., 2010) to assess reliability of information. The structure of the questionnaire, the repeat questions/sham questions and the testing context allow for significant confidence interval in the validity of the self-reported data.

Quality control flag applied:

On the primary outcome

- For the DEP-ADO, those who answered positively to the fake drug item (DEPADO Foil) were flagged and 0.4% of DEP-ADO Drug records were rejected.
- Secondly, those who report uncommon substance use (sum of (TRANQ, STEROIDS, SPEED, PCP, LSD, HEROIN, ECSTASY)>2.5) were also flagged and 0.1% of records were rejected.
- The SURPS results should indicate a minimum of variation. In the absence of variation in the answers, results were flagged and 0.4% of records were rejected)

On the secondary outcomes:

- CFT - There seems to be a significant year to year learning effect in this task (0.1% of CFT records rejected)
- The PALP's "worse than chance" QC flag identifies and excludes those with more than 30 commissions or with more than 30 omissions. With that flag, 17.6% of records were rejected.
- Just like the SURPS, if there was no variation in the SDQ answers, answers were rejected and 0.6% of records were rejected).
- For the CMS task, the time duration between the first part and the recall should not be negative, or longer than the time allotted in a period of class

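### SAP 26.b bases its follow-up time-point tests on the Huber-White sandwich with 31 schools but gives no small-sample correction or degrees of freedom; the plain version rejects at about 7-9.5% per test, not 5%

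*Combined protocol and SAP*

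**What the plan says.** SAP 26.b (Supplementary analysis methods used for the primary outcome) fits a growth model for substance use disorder over 12 to 48 months. A second step follows: "When significant effects are revealed on growth, analyses will be conducted". That step tests intervention effects "at specific time points while controlling for cluster, using tests based on the Huber-White sandwich estimate of variance". SAP 26.c (Analysis methods used for the secondary outcomes) carries a like approach over to alcohol and drug use and the other Appendix 3 outcomes. Protocol 2.16 has the same two-step scheme and also says that "HLM with robust standard errors will be used to assess intervention effects on the 12-month intercept and growth in drinking".

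Four other places set the conditions for these tests:

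- **Level.** SAP 15: "All applicable statistical tests will be two-sided and at the 5% significance level". SAP 16 plans no multiplicity adjustment.
- **Clusters.** SAP 20 describes the cohort as "76% of all grade 7 students attending 31 secondary schools in the greater Montreal area". Table 2 in SAP 18.a lists 15 intervention schools with 14 to 86 high-risk students each.
- **Covariates.** SAP 26.b (Adjustments) puts school language and three-category gender mix into every model and adds immigration status as a student-level covariate.
- **Later change.** Item 6 of the deviations list that closes the SAP moves to a Bayesian multilevel model. The model code printed there for the primary outcome contains no sandwich test.

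Nowhere is a small-sample correction, a number of degrees of freedom or a reference distribution given for the sandwich tests.

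**The concern.** The sandwich variance is justified as the number of clusters grows. It is built from fitted residuals, which are smaller than the true errors because each school pulls the fit towards itself. With few schools, unequal sizes and several school-level parameters, the variance is too small on average and also noisy. The test then rejects too often, and the confidence interval is too narrow.

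These tests are the ones that would support a statement that the programme worked at a given follow-up year. If such a statement is reported at a nominal 5% from the plain sandwich, its stated error rate is wrong. If the correction is chosen only after the data are seen, the choice itself can decide significance.

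**Working it through.** **1. Planning inputs and the plan's own figure.** SAP 10 uses 10% v 5%, k = 0.35, 50 students per school, 80% power and a false-positive rate of 2.5%. The standard formula for comparing proportions in a cluster trial is

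c = 1 + (z_α + z_β)² [p0(1−p0)/m + p1(1−p1)/m + k²(p0² + p1²)] / (p0 − p1)²

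= 1 + 7.849 × [0.0018 + 0.00095 + 0.00153] / 0.0025 = 14.44, so 15 schools per arm, as stated. This holds with 2.5% in one tail, that is, a two-sided 5% test. The 10% rate and k = 0.35 are therefore usable as inputs.

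**2. Design as run.** There are 31 schools, 15 intervention (Table 2) and hence 16 control. Table 2 sizes sum to 709, with mean 47.3 and coefficient of variation 0.40. School-level parameters: intercept, arm, language (1) and gender mix (2), which makes 5. Degrees of freedom: 31 − 5 = 26.

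**3. Hand approximation, equal schools.** Suppose that the plain variance is too small by about (G − p)/G and that the ratio behaves like t on G − p.

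- With covariates: √(26/31) = 0.916. Normal reference: P(|t26| > 1.96 × 0.916 = 1.795) = 8.4%. t reference: P(|t26| > 2.056 × 0.916 = 1.882) = 7.1%.
- Arm only: √(29/31) = 0.967. Normal reference: P(|t29| > 1.896) = 6.8%. t reference: P(|t29| > 1.978) = 5.7%.

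**4. Simulation under no effect.** Beta-binomial outcomes, logistic model, school-clustered sandwich, two-sided 5%, 12,000 replicates (Monte Carlo SE about 0.25 points). Assumed: control-school sizes drawn from Table 2, 8 of 31 schools in the minority language, and 4 + 4 in the two extreme gender categories, spread evenly over the arms. Rejection rates in %, school covariates in the model:

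| Scenario | Plain, normal | Plain, t26 | G/(G−1) factor, normal | Kauermann-Carroll, t26 | Mancl-DeRouen, t26 |
|---|---|---|---|---|---|
| 10%, k = 0.35, Table 2 sizes, independence weighting | 9.2 | 7.9 | 8.8 | 5.2 | 3.4 |
| Same, exchangeable weighting | 9.1 | 7.6 | 8.6 | 5.2 | 3.3 |
| Same as first row, equal schools of 50 | 8.2 | 6.8 | 7.6 | 4.7 | 3.1 |
| 5% event rate, exchangeable weighting | 8.9 | 7.6 | 8.5 | 5.2 | 3.3 |
| First row plus immigration status | 9.4 | 8.0 | 8.9 | not run | not run |
| First row with k = 0.7 | 10.3 | 8.9 | 9.9 | 5.9 | 3.6 |

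Without covariates, the plain sandwich gave 6.8-7.5% with a normal reference and about 6% with t.

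**5. Other assumptions.** With 80% of Table 2 sizes, school SD 0.36-0.57 on the logit scale, language split 22/9 and gender mix 5/20/6, the plain sandwich gave 9.3-10.5% (normal) and 8.5-9.0% (t26); a leverage-corrected version with t26 gave 5.5-6.2%. A further run with k = 0.35-0.5 gave 8.5-8.9%, 7.3-7.6%, and 5.3-5.4% for Kauermann-Carroll with t.

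The direction is the same throughout. A t reference alone does not restore 5% once the school covariates are in, and neither does the G/(G−1) factor. Kauermann-Carroll with t comes close to 5% at the planned k. Mancl-DeRouen with t overshoots to about 3%.

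**The case against.** Several points on the other side stand.

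- **The SAP does not choose an uncorrected estimator.** It names the sandwich family and is silent on the version. A reader might infer a stated choice of the plain form; the text shows only an omission. The omission still matters, because the plain form satisfies the wording.
- **The tests are gated and supplementary.** If there is no effect at all and the growth test holds its 5% level, a false time-point claim for a given outcome cannot arise more often than the gate opens, about 5%. The gate does not repair the standard error, though. When growth truly differs, tests at years without an effect carry the inflated rate, and the intervals are too narrow in either case.
- **The primary analysis is untouched.** SAP 26.a is a two-level model at 48 months with no sandwich specified. SAP 16 treats secondary endpoints as exploratory support.
- **For the primary outcome the issue is largely overtaken.** The categorical-time Bayesian model at the end of the SAP gives year-by-arm effects with a school random effect and no sandwich. But that code covers only the primary outcome, and the wording of 26.b and 26.c has not been withdrawn.
- **The simulated model is not exactly the planned one.** SAP 26.b speaks of a hierarchical model; the simulation is a marginal logistic model, as in the older protocol 2.16 text for this step. The percentages are therefore approximate.

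**Conclusion.** The point holds as a gap in specification with a measurable consequence. With the school covariates that the SAP requires, the plain sandwich has a per-test false-positive rate of about 8.5-9.5% with a normal reference and about 7-9% with a t reference, against a stated 5%. The corresponding 95% intervals would cover roughly 91-93% of the time. Without covariates the rate is about 6-7.5%.

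Rates above 10% arose at k = 0.7, twice the planned value, and at the top of the range in the logit-scale runs. They should not be taken as the expected figure. Nor do the documents support reading 9-10% as the trial's type I error or as a flaw in the 48-month primary result: the affected tests are conditional and supplementary, and the primary test does not use this estimator.

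The size rests on assumed control-school sizes, assumed language and gender splits, and a marginal logistic model in place of the hierarchical fit. The direction does not depend on those details.

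**What to change.** For every sandwich-based time-point test that will still be reported, under SAP 26.b and for secondary outcomes under 26.c, state three things: the Kauermann-Carroll bias-corrected sandwich, a t reference, and degrees of freedom equal to schools minus school-level parameters (31 − 5 = 26). Name the correction explicitly. Mancl-DeRouen with t is not an equivalent substitute, because it was conservative here (about 3%).

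Where the Bayesian categorical-time model replaces these tests, say in 26.b that the sandwich tests are withdrawn, and say which outcomes this covers.

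The cost is a sentence or two in the SAP, one setting in the analysis code, and slightly wider intervals. No new data are needed, and the primary analysis does not change.

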**26.c Analysis methods used for the secondary outcomes**

Using a similar method, secondary analyses will examine the 12-month intercept and the linear slopes (i.e. growth) from 12 - 48 months post-intervention between intervention and control conditions in alcohol and drug use behaviours. Growth terms will be used to detect prevention effects on growth in substance use behaviours over 4 years.

Similar analyses will be carried out for secondary and exploratory outcomes presented in Appendix 3.

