Our research team has now repeatedly and consistently shown that psychological interventions targeting personality risk factors for substance misuse are highly effective in preventing and reducing alcohol and drug use in adolescents. Beneficial effects of the Preventure programme on substance use outcomes have been replicated in three separate trials in Canada [27] and the United Kingdom [25, 26, 28, 69], showing 30%-80% reductions in drinking, binge drinking and illicit drug use, and onset of problem symptoms over a two-year period. The Preventure programme has proven both feasible and effective when delivered by trained school-staff [28], and thus can operate within an implementation model that has a higher likelihood of being adopted by schools in a sustainable manner. We now aim to show impact of the programme on socially and clinically significant outcomes.

This study provides a unique opportunity to examine the beneficial effects of early intervention on cognitive development and future addiction, while controlling for neuropsychological factors implicated in the predisposition to early onset drinking. The outcomes of this trial are dually relevant for etiologic theories of addiction and for translating research to practice in real-world and sustainable ways.

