### *2.9 How will the outcome measures be measured at follow up?*

Follow-up outcomes for self-report and cognitive measures will be assessed using the same measures as the initial assessment, in class sessions at 12-months intervals for 4 years. A computerised web-based data-acquisition platform will be used to collect self-report and cognitive data. Researchers will bring electronic Netbooks to classrooms and will assess whole grades of students at a time. Netbooks will allow us to avoid any scheduling difficulties associated with trying to use the school computer laboratories. Should students be absent from follow-up sessions, efforts will be made to organise additional data collection sessions at the school. Academic and attendance data will be requested from the school each year. Parallel forms of neuropsychological tasks will be used across repeated measurements, counterbalanced for order of presentation, to address potential learning effects, but most concerns around repeated assessment are addressed by random allocation to intervention groups. The data monitoring committee will pilot parallel tasks prior to data collection to detect possible ceiling effects.

In year 3 and in year 4 of follow up in data assessment, we will be asking the Ministry of Education their collaboration threw the "Comité d'Accès à l'Information" to access the grades of all the participants in this study obtained on their ministry exams done in grade 9 and in grade 10. By having access to the ministry grades, we will be able to measure whether our intervention has a positive effect on child cognitive development since the ministry exams are associated to cognitive development in child development as well. Therefore we can demonstrate following our analyzes whether the intervention has a positive effect on the ministry grades by comparing them to the control group and thus promote the implementation of the program Preventure in schools and overlook this positive outcome. We have decided to use the ministry exams as a measure of outcome on cognitive development since it's an homogenous tool across our whole sample data.

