### **26.b Adjustments for primary and secondary outcomes**

To take into account the baseline prognostic factors at the cluster (school) level used for DA (c.f. Section Randomisation), all the results will be adjusted for language of the school, and the gender with three categories.

In case of imbalance for a variable at baseline, interaction and confounding effects will be tested according to its clinical significance.

Modification to protocol: Considering that immigration status has a very large protective effect on youth substance use (including in this sample), and that schools in Montreal vary significantly on this variable, we have modified the analysis plan to also include immigration status (immigrant, first generation, second generation) as a covariate.

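### The secondary cognitive and mental-health models do not pre-specify the outcome's own Grade 7 score, which loses precision and leaves the 12-month contrast open to chance school imbalance

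*Combined protocol and SAP*

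**What the plan says.** - **Model.** SAP 26.c (Analysis methods used for the secondary outcomes) states that "secondary analyses will examine the 12-month intercept and the linear slopes (i.e. growth) from 12 - 48 months post-intervention". That sentence goes on to name alcohol and drug use. Cognition and mental health are reached through the section's last sentence: "Similar analyses will be carried out for secondary and exploratory outcomes presented in Appendix 3". Table 3 in Appendix 3 lists these outcomes for Grades 8 to 11 only. Protocol 2.16 has the same structure: "Secondary outcome variables will be centred at the 12-month post-test to allow for comparisons between groups".
- **Covariates.** SAP 26.b (Adjustments for primary and secondary outcomes) says that "all the results will be adjusted for language of the school, and the gender with three categories", and then adds immigration status. No outcome's own baseline value is listed.
- **Baseline data exist.** SAP Table 1 marks the cognitive tasks and mental-health symptoms at baseline. Protocol 2.9 says: "Follow-up outcomes for self-report and cognitive measures will be assessed using the same measures as the initial assessment".
- **Conditional use of baseline.** SAP 26.b (Adjustments) adds: "In case of imbalance for a variable at baseline, interaction and confounding effects will be tested according to its clinical significance". SAP 24.b allows, but does not require, adjusted sensitivity analyses if a substantial imbalance is found. Neither clause gives a threshold or a model. SAP section 4 (Description of this document) says that the analyses are not blind to randomised group.
- **Aim.** Protocol 1.3 describes the study as examining effects "while controlling for neuropsychological factors implicated in the predisposition to early onset drinking".

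**The concern.** About 30 schools are compared, and SAP section 9 balances allocation on language and gender category only. By chance, the schools in one arm may already score higher in Grade 7 on, say, the reasoning task. If school differences persist, that gap reappears in the 12-month intercept contrast, and a model without the Grade 7 score cannot separate it from an intervention effect.

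The Grade 7 score is also likely to be among the best available predictors of the later score. Leaving it out widens the interval for the cognitive question named in the trial's title. The conditional clauses leave the decision to adjust until after baseline has been inspected, in an analysis that is not blind to group.

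**Working it through.** **Inputs.** SAP section 10: 15 schools per arm, 50 high-risk students per school, difference 3.0, SD 15.0 (d = 0.20), ICC 0.40, false positive rate 2.5%, power at least 90%. SAP section 15: two-sided 5% tests. Protocol 2.11: ICC 0.09 for problem drinking, used here as a low scenario because protocol 2.16 does not expect high cognitive ICCs. The correlation between baseline and follow-up is not given in the documents; the values below are assumptions.

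**The plan's own power figure.** Design effect = 1 + 49 × 0.40 = 20.6. Effective students per arm = 750 / 20.6 = 36.4. SE = 15 × √(2/36.4) = 3.52 points. By the normal approximation, power for 3.0 points is about 8% at two-sided 2.5% and about 13% at two-sided 5%. The stated 90% does not reproduce; it would need an ICC of about 0.004 to 0.009. That is a separate defect, but it means that the cognitive analyses have little precision to spare.

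**Unadjusted SE in SD units, one wave, planned covariates left out.** Var = (2/15)[ICC + (1 − ICC)/50].

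- ICC 0.40: (2/15)(0.40 + 0.012) = 0.0549, SE 0.234. The between-school share is 0.40/0.412 = 97%.
- ICC 0.09: (2/15)(0.09 + 0.0182) = 0.0144, SE 0.120.

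**Chance baseline gap of 0.20 SD or more, either direction.** ICC 0.40: P(|Z| ≥ 0.20/0.234) = 39%. ICC 0.20: 24%. ICC 0.09: 10%.

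**With the Grade 7 score as student deviation plus school mean.** Var = (2/15)[ICC(1 − r_s²) + (1 − ICC)(1 − r_i²)/50], where r_s is the school-mean correlation and r_i the student-level correlation. Power is from the noncentral t at two-sided 5%, with 28 df unadjusted and 27 adjusted.

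| ICC | r_s / r_i (assumed) | SE unadjusted | SE adjusted | Power unadjusted | Power adjusted |
|---|---|---|---|---|---|
| 0.40 | 0.5 / 0.5 | 0.234 | 0.203 | 13.1% | 15.8% |
| 0.40 | 0.7 / 0.7 | 0.234 | 0.167 | 13.1% | 21.1% |
| 0.40 | 0.9 / 0.7 | 0.234 | 0.105 | 13.1% | 45.4% |
| 0.20 | 0.5 / 0.5 | 0.170 | 0.147 | 20.7% | 25.9% |
| 0.09 | 0.5 / 0.5 | 0.120 | 0.104 | 36.3% | 45.8% |
| 0.09 | 0.9 / 0.7 | 0.120 | 0.059 | 36.3% | 90.1% |

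**Type I error.** This was checked with 40,000 simulated null trials on school means per setting, at ICC 0.40, r_s 0.8 to 0.95 and r_i 0.5 to 0.7. Overall rejection was 5.0 to 5.2% unadjusted and 5.0 to 5.1% adjusted. Among trials in which baseline favoured one given arm by 3 points or more (about 19 to 20% of them), the unadjusted follow-up contrast averaged 4.0 to 4.7 points with 12 to 13% rejection. The adjusted contrast averaged about 0 with 4.5 to 4.9% rejection.

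**Slope.** Write the arm difference at month t as a + b(t − 12). A constant pre-existing gap g gives a = g and b = 0, so it moves the intercept and not the 12 to 48 month slope.

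**The case against.** Several stronger readings are tempting, and the documents do not support them.

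- **That baseline is never used.** SAP 26.b (Adjustments) says that imbalance will lead to testing of confounding, and SAP section 24 tabulates baseline outcomes by arm and has them inspected by school. What stands is narrower: the route is conditional, has no stated trigger or model, and does not replace a pre-specified covariate.
- **That the estimate is biased.** Schools are randomised and the model has a school level, so overall type I error is near 5%. The exposure is to chance imbalance in the one allocation that occurred.
- **That the 12-month contrast is a raw comparison.** It is adjusted for language, gender category and immigration status. The 0.234 SD and 39% leave these out, so they are upper-end figures if those factors explain school variance.
- **That the development question as a whole is affected.** A stable level difference cancels from the slope, which is half of the planned test and the part closest to growth.
- **That protocol 1.3 commits the team to baseline adjustment.** It is rationale about the design, not a model specification.

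It is also fair to say that SAP section 16 treats the secondary endpoints as supportive and exploratory, that an ICC does not show whether school means are stable over time, and that the gain at ICC 0.40 with correlation 0.5 is only about 3 points of power. These limit the weight of the point but do not remove it. The model code at the end of the SAP concerns the primary outcome and does not fill the gap.

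**Conclusion.** The point holds as one about precision and chance imbalance. The Grade 7 scores are collected, yet they are neither a modelled wave nor a pre-specified covariate for the cognitive and mental-health outcomes. The 12-month intercept contrast bears the consequence.

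The size depends on two quantities that the plan leaves open. One is the ICC, where 0.40 in SAP section 10 sits badly with protocol 2.16. The other is the baseline correlation. At a correlation of 0.5, variance falls by 25% at any ICC, which is worth about 3 points of single-wave power at ICC 0.40 and about 10 points at ICC 0.09. Gains are much larger if school means are stable. The calculations treat one wave with equal school sizes, not the full repeated-measures model. For supportive outcomes this is a worthwhile and inexpensive improvement, not a threat to validity.

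**What to change.** In SAP 26.c (secondary outcomes) and SAP 26.b (Adjustments), choose and state one of two models for each continuous secondary outcome (CFT, CMS, PALP, working memory, SDQ, BSI):

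1. Add the outcome's own Grade 7 score as two covariates: the student's deviation from the school mean, and the school mean. These main effects adjust level only. If the slope is also to be adjusted, add their interactions with time.
2. Model all five waves with the arms constrained equal at baseline, and with school and student effects that can correlate across waves.

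State that this applies whether or not imbalance is seen, in place of the conditional clause for these scores.

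No new data are needed, since SAP section 19 requires a completed baseline survey. The cost is about one school-level degree of freedom and a few more terms per outcome. Missing baseline scores need a stated rule. SAP section 20 reports that 17.6% of PALP records were rejected, and the SAP's closing list of deviations reports that multiple imputation did not converge. The five-wave model handles missing baseline scores without a separate imputation step, under a missing-at-random assumption. Because SAP 18.d records an item added to the CMS in years 3, 4 and 5, standardise that score within wave.
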